# Proper Handling of Subjects

## Ethical Considerations

Cognitive testing may reveal undiagnosed cognitive impairments.

## Subject Withdrawal

### Early Withdrawal of Subjects

We will track the number of withdrawn subjects. Possible reasons a subject may withdraw are a desire to discontinue their participation, or a deterioration in clinical condition or level of consciousness to the point where the patient can no longer participate.

### When and How to Withdraw Subjects

A withdrawal occurs when a subject voluntarily chooses to leave or is no longer able to participate in the research study. We will remove a subject if they mention to the research personnel that they no longer wish to continue with the study or when the research personnel note that, for medical reasons, the subject is no longer able to participate. The research personnel will keep all personal health information secured in the database.

### Data Collection and Follow-up for Withdrawn Subjects

We will not store data or follow-up after subject withdrawal.

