#### Delirium Assessment

We will administer the Confusion Assessment Method (CAM) on postoperative days 1 and 2. The CAM is a validated assessment tool for the diagnosis of delirium^56^ and is based on the diagnostic criteria for delirium from the Diagnostic and Statistical Manual of Mental Disorders (DSM). The cognitive testing on postoperative days 1 and 2 will consist of basic orientation questions and a sustained attention task (stating the months of the year backwards). If the CAM yields a positive diagnosis, we will administer a subsequent test, the CAM-S which assesses the severity of delirium. In the case of persistent mechanical ventilation after surgery in the ICU, we will administer the Intensive Care Unit version of the CAM (CAM-ICU)^57^.

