### Endpoints

#### Primary Endpoint

- Incidence of major NCD at postoperative day 1.

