## Statistical Methods

### General Considerations

Descriptive statistics will be presented by groups using mean (SD) or median (Q1, Q3) for continuous parameters (according to the skewness or not of the distribution of each parameter), and frequency (%) for categorical parameters. According to the nature of the analyzed endpoints, confidence intervals (CIs) between proportions or between means/medians differences will be presented. The alpha value will be set a 0.05. All data will be analyzed by the intention to treat principle. All statistical analysis will be performed using SAS, SPSS or R software.

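### Patients who become medically unable to take part are handled like patients who withdraw consent, so outcome-related loss is written into a cognitive trial

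*Protocol*

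**What the plan says.** Section F.2.1 (Early Withdrawal of Subjects) gives two possible reasons for withdrawal: the patient's own wish, and "a deterioration in clinical condition or level of consciousness to the point where the patient can no longer participate". Section F.2.2 does not require a request from the patient. Removal also happens "when the research personnel note that, for medical reasons, the subject is no longer able to participate". Section F.2.3 is a single sentence: "We will not store data or follow-up after subject withdrawal". It makes no distinction between the two reasons.

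Section F.2.2 also says of information already collected: "The research personnel will keep all personal health information secured in the database". Section F.2.1 says that the number of withdrawn subjects will be tracked.

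Four other places bear on this:
- The primary endpoint (D.6.3.1) is "Incidence of major NCD at postoperative day 1". Section D.6.1.1 scores it from the MoCA before anesthesia and at 24 hours after surgery.
- Section G.2.1: "All data will be analyzed by the intention to treat principle".
- Section D.6.2.2: "In the case of persistent mechanical ventilation after surgery in the ICU, we will administer the Intensive Care Unit version of the CAM".
- Section G.1 inflates 282 patients to 314 for 10% withdrawals and loss to follow-up, and says nothing else about them.

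**The concern.** The trial measures cognitive decline. A falling level of consciousness after surgery is close to the outcome itself, and it arises after randomisation. A rule under which staff remove such patients and stop observing them therefore makes the chance of being observed depend on the outcome.

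What is lost depends on when the patient is removed:
- **Before the day 1 MoCA:** the primary outcome and everything after it.
- **After the day 1 MoCA:** the primary outcome is safe. NCD at the remaining visits up to day 90, any later delirium assessment, the trajectory data and QoR-15 at days 30 and 90 are lost.

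If true cases are removed in similar proportions in both arms, the observed difference shrinks and power falls. If the proportions differ between arms, a difference can be created or hidden.

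**Working it through.** **1. The plan's own figure.** Inputs from G.1: 15% versus 5%, two-sided alpha 0.05, power 80%. With the pooled-variance formula for two proportions:

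n = [1.960 × √(2 × 0.10 × 0.90) + 0.842 × √(0.15 × 0.85 + 0.05 × 0.95)]² / 0.10² = 140.1, rounded up to 141 per arm, 282 in total.

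141 / 0.90 = 156.7, rounded up to 157 per arm, 314 in total. Both stated figures reproduce. The exact power of the Pearson chi-square test is 82% at 141 per arm and 86% at 157.

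**2. Scale of the allowance.** The allowance is 314 − 282 = 32 patients. Expected primary events among 282 are 141 × 0.15 + 141 × 0.05 ≈ 21 + 7 = 28. The allowance is thus about as large as the whole event count, so it matters who the lost patients are.

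**3. Removing a fraction f of true day 1 cases in each arm.** Assumptions: 15% and 5% are the rates in all patients, and f is not given in the protocol. The observed rate is p(1 − f) / (1 − pf), and the patients left are n(1 − pf). For f = 1/3:

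- Control: 0.15 × 0.667 / 0.95 = 10.5%
- EEG-guided: 0.05 × 0.667 / 0.983 = 3.4%
- Difference: 7.1 points instead of 10

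| f | Observed rates | Difference | Exact power from 141 per arm (patients left) | Exact power from 157 per arm (patients left) |
| --- | --- | --- | --- | --- |
| 0 | 15% vs 5% | 10 points | 82% | 86% |
| 0.1 | 13.7% vs 4.5% | 9.2 points | 79% (139/140) | 83% (155/156) |
| 1/3 | 10.5% vs 3.4% | 7.1 points | 66% (134/139) | 71% (149/154) |
| 0.5 | 8.1% vs 2.6% | 5.5 points | 56% (130/137) | 61% (145/153) |

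The 157 column assumes that these removals are the only losses. The 141 column assumes that the 10% allowance has already been used up by unrelated losses.

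**4. Unequal removal with no true effect.** Take 12% in both arms and remove 10% of cases in one arm and 40% in the other (assumed):

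- 0.12 × 0.9 / (1 − 0.012) = 10.9%
- 0.12 × 0.6 / (1 − 0.048) = 7.6%

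This is a false difference of 3.4 points before rounding of the two rates. Starting from 141 per arm (139 and 134 left), the exact type I error is about 16% instead of 5%.

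**5. The direction is not fixed.** If instead the same share of each whole arm is removed, say 2%, and all of these patients are true cases, the rates become (0.15 − 0.02) / 0.98 = 13.3% and (0.05 − 0.02) / 0.98 = 3.1%. The difference of 10.2 points is hardly changed, but both incidences are understated.

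**The case against.** A reader might infer that the worst outcomes are deleted from the primary endpoint beyond any repair. The protocol does not support that. F.2.3 stops storage and follow-up only after withdrawal, and F.2.2 keeps what is already held. Arm, baseline MoCA and any day 1 MoCA already done therefore remain. For a patient removed before day 1, an analysis plan could still set a scoring rule or a worst-case analysis, and a scoring rule would need only the reason for removal. What cannot be recovered is later follow-up.

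A reader might also infer that anyone who misses the day 1 MoCA is thereby withdrawn. F.2.1 speaks of no longer being able to participate, and a missed test is not said to be a withdrawal. The CAM-ICU provision shows that at least some untestable patients are expected to stay under assessment. It can be read as limiting the removal rule. The protocol does not say where the limit lies, so the sections still need reconciling.

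A flat contradiction of intention to treat would be too strong as well. That principle can be met in the narrow sense of analysing patients in the arm assigned, and handling of missing outcomes is commonly left to an analysis plan. The tension remains, because staff-initiated removal without follow-up prevents outcomes from being observed in randomised patients.

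The numbers also have limits. The planning rates in G.1 come from patients tested with the MMSE before and 24 hours after surgery. If untestable patients were not in those rates, 15% versus 5% already describes testable patients and the deflation in step 3 does not apply. At f = 0.1 with no other loss, the planned 80% power is still met. Nothing in the protocol points to a fourfold difference in removal between arms. Not every medical deterioration is cognitive.

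**Conclusion.** The point holds as a defect in a stated rule. Sections F.2.1 to F.2.3 apply to medically incapacitated patients a no-follow-up rule that suits only withdrawal of consent. Followed as written, this produces loss after randomisation that is plausibly related to the outcome. It affects the primary endpoint for patients removed before the day 1 MoCA, and the later endpoints for everyone removed. It fits poorly with G.2.1 and D.6.2.2.

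The size of the bias is unknown and its direction is not fixed. Under the stated assumptions, removing 10% to 50% of true cases gives exact power of 79% to 56% from 141 per arm, or 83% to 61% from 157. The differential example gives a type I error of about 16%. These figures show sensitivity to assumed removal fractions and do not predict what will happen. The case for change rests on the wording of the rule and on the irrecoverable later data.

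**What to change.** 1. In F.2.1 to F.2.3, limit withdrawal to withdrawal of consent, and keep the data collected up to that point.
2. Keep patients who are medically unable to be tested in follow-up. At each visit, record why a test was not done: impaired consciousness or delirium, ventilated, other medical reason, refusal, death.
3. Prespecify how a patient untestable on day 1 enters the primary analysis, with a sensitivity analysis under the alternative handling. One option is to count patients untestable because of impaired consciousness, positive CAM or CAM-ICU, or death as major NCD. That option has a price: the endpoint becomes partly composite and departs from the pure MoCA Z-score definition in D.6.1.3, it overlaps the delirium secondary endpoint, and the 15% versus 5% assumption would need rechecking.
4. Reconcile F.2.1 to F.2.3 with D.6.2.2 and G.2.1.

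Items 1, 2 and 4 cost amendment wording and one reason-not-done field on the CRF, with no visits beyond those already scheduled. They have to apply prospectively, because assessments not made at the time may not be recoverable. Item 3 needs a decision by the trial team.

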## Risks

There is very little added risk involved with participation in this study and the protocol is not expected to increase duration of anesthesia. The anesthetic care provided will be routine, we will use standard intraoperative monitoring, and only use common analgesics, such as intravenous remifentanil.

# Statistical Plan

## Sample Size

In a previous study at HMR/CEMTL, we evaluated as an exploratory outcome NCD in a population (mean age of 65) undergoing major colorectal surgery under general anesthesia. We established the incidence of major NCD (using pre- *versus* 24h after surgery MMSE testing; Z score ≥ 1.96 SD in MMSE evaluations pre and postoperatively) at postoperative day 1 was 3.8% in the monitored group (EEG-guided anesthesia with BIS index) versus 15.4% in the control group (standard of care group, BIS placed but not used to guide intraoperative administration of the halogenous gas). Similar results had also been observed by Hou R. et al. in 2018^61^. Based on a 2-sided α <0.05 and 80% power, we calculated that the enrolment of 282 patients was required to detect (as the primary endpoint of the proposed study) a clinically significant and relevant reduction of at least reduction of 10% of NCD incidence in the EEG-guided group compared to the control group (expected decrease from 15% to 5% or less). The sample size will be inflated to 314 (157 in each group) to account for 10% withdrawals and loss of follow-up.

## Statistical Methods

### General Considerations

Descriptive statistics will be presented by groups using mean (SD) or median (Q1, Q3) for continuous parameters (according to the skewness or not of the distribution of each parameter), and frequency (%) for categorical parameters. According to the nature of the analyzed endpoints, confidence intervals (CIs) between proportions or between means/medians differences will be presented. The alpha value will be set a 0.05. All data will be analyzed by the intention to treat principle. All statistical analysis will be performed using SAS, SPSS or R software.

### Primary Analysis

Incidence of NCD will be presented using frequency and proportion (%), broken down by groups (EEG use or SOC). The distribution of presence or absence of NCD will be compared between the two groups using a chi-square test. A risk difference will be reported with a score (Wilson) 95% confidence interval.

In a case we observe important quantitative imbalance between prognostic factors between the treatment groups, we will conduct an adjusted analysis of the primary outcome. We will estimate a standardized marginal average treatment effect (risk difference) model adjusted from 10 strata based on an estimated propensity score from NCD risk factors (age, sex, preoperative MoCA score, CFS, PHQ-9 and education level). The marginal risk difference will be reported with 95% confidence intervals, estimated by non-parametric bootstrap (10 000 replications).

### Secondary Analysis

Presentation of results and group comparisons (EEG use or SOC) for the secondary dichotomous endpoints will be done using the same approach described in the primary analysis. For the continuous endpoints, the group comparisons will be done using a t-test or a Mann-Whitney-Wilcoxon test according to the distribution of each parameters and a chi-square test will be used for proportion. Risk differences or mean differences with 95% confidence intervals will be reported for all outcomes.

### Trajectories Analysis

Z scores of T-MoCA and T-MoCA part of the MoCA test (baseline, D1, D2, D7, D15, D30 and D90) will be entered in a group-based trajectory model (GBTM) to derive trajectories of cognitive function. GBTM allows for the identification of patient subgroups sharing similar cognitive patterns over time^62,63^. Different models will be tested that vary based on the number of trajectories (models that contain between 1 and 8 trajectories will be tested) and inclusion of linear and quadratic terms. Selection of the final model is based on Bayesian Information Criteria (BIC), parsimony, and ≥ 5% of patients in each class. Once the final model is selected, outcome variables represent probabilities of belonging to each of the trajectories. For each of the relevant baseline variables, the GBTM obtained will be rerun with the inclusion of age, sex, randomization group and education as covariates. For each model, an odds ratio will allow for the examination of the contribution of the variable of interest to the classification of patients in each trajectory.

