## Research plan and timeline

Patients will be screened at the preoperative clinic. The day of the surgery (D0), after signing the consent form, patients will undergo the inclusion visit. Cognitive assessment will be performed using the MoCA and verbal fluency tests by a trained research team. Patients will also be screened for depression and frailty. The patient will then be randomized in the EEG-guided or SOC group.

Postoperative visit will be performed at postoperative days 1 and 2 (D1 and D2). Cognitive assessments will be performed using MoCA and verbal fluency tests. Patients will also be screened for postoperative delirium.

Once patients return home, phone interviews will be done at D7, D15, D30 and D90. Cognitive assessments will be performed using the telephone version of the MoCA (T-MoCA) and verbal fluency tests. Quality of recovery will be evaluated at D30 and D90 using the QoR-15 questionnaire.

T-MoCA and T-MoCA part of the MoCA as well as verbal fluency will be used to establish cognitive trajectories of the two groups.

The 3 versions of the MoCA will be alternately and randomly used to limit learning effect.

Estimated time for each visit is approximatively 45 minutes. The study timeline used tests and expected cognitive trajectories are presented in figure 1.

All the tests are provided in the references and detailed below. These tests are also attached in the annexes in French and in English.

[figure not shown]

**Figure 1. Study timeline, tests and expected cognitive trajectories**. *MoCA: Montréal Cognitive Assessment; PHQ-9: Patient Health Questionnaire 9; CFS: Clinical Frailty Scale; EEG: electroencephalograph; SOC: Standard of Care; CAM: Confusion Assessment Method; QoR: Quality of Recovery; T-MoCA: Telephone MoCA.*

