#### Z Scores and Definition of Neurocognitive Disorders (NCD)

We will calculate Z scores for individual tests - (Verbal fluency, MoCA, T-MoCA) at each testing time point with the mean and standard deviation (SD) of baseline tests of all patients - in the following way:

$$Z_{test}=\frac{x_{test}-\mu_{test baseline}}{\sigma_{test baseline}}$$

where $x$ corresponds to individual test value, $\mu$ and $\sigma$ correspond to test mean and SD of all patients at baseline respectively.

We will use MoCA Z scores (or T-MoCA depending on the testing time point) to define NCD. Neurocognitive disorders will be classified as mild or major^12,15^:

- **No NCD**: a decrease in Z score < 1 SD,
- **Mild:** a decrease in Z score ≥ 1 SD,
- **Major:** a decrease in Z score ≥ 1.96 SD.

| Z score decrease | Postoperative days 1,2,7,15, 30 and 90 |
| --- | --- |
| < 1 SD | No NCD |
| ≥ 1 SD and < 1.96 SD | Mild NCD |
| ≥ 1.96 SD | Major NCD |

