#### Secondary Endpoints

- The incidence of major NCD at postoperative day 2, 7, 15, 30 and 90
- The evolution over time in cognitive assessment scores defining cognitive trajectories,
- The incidence of postoperative delirium during hospital stay,
- The total intraoperative consumption of volatile anesthetics, opioids and vasopressors over surgery time
- The incidence of intraoperative hypotension,
- The incidence of cerebral hypoxemia,
- The cumulative burst suppression duration and low BIS values duration during anesthesia,
- The incidence of awareness,
- The difference between quality of recovery scores between groups.

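### The trajectory analysis models score levels, with the pre-randomisation baseline as an outcome and at most quadratic time, so its odds ratio for arm is poorly suited to showing a treatment effect on an early, transient cognitive fall

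*Protocol*

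**What the plan says.** Secondary Endpoints lists "The evolution over time in cognitive assessment scores defining cognitive trajectories", and Secondary Objectives asks for the effect of EEG guidance on those trajectories. Trajectories Analysis sets out the method:

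- **Response:** "Z scores of T-MoCA and T-MoCA part of the MoCA test (baseline, D1, D2, D7, D15, D30 and D90) will be entered" in the GBTM.
- **Scaling:** under Z Scores and Definition of Neurocognitive Disorders, the centring and scaling constants "correspond to test mean and SD of all patients at baseline respectively". A patient's own baseline is not subtracted, so each Z score is a level.
- **Time:** candidate models vary in the "inclusion of linear and quadratic terms". No higher-order, spline or visit-specific term is mentioned, and the time scale (days or visit number) is not given.
- **Classes:** "models that contain between 1 and 8 trajectories will be tested", with selection on "Bayesian Information Criteria (BIC), parsimony, and ≥ 5% of patients in each class".
- **Arm:** "the GBTM obtained will be rerun with the inclusion of age, sex, randomization group and education as covariates", reported as odds ratios for class membership. The baseline score is not a covariate.

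Research plan and timeline puts baseline testing first: "The patient will then be randomized in the EEG-guided or SOC group".

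**The concern.** There are two separate problems.

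1. A standard GBTM has no random intercept within a class, so stable differences between patients have to be absorbed by the classes. With level scores the classes therefore tend to become high, middle and low cognition. Much of that is already set before randomisation and is balanced between arms, so the arm cannot predict it.
2. The visits fall on days 0, 1, 2, 7, 15, 30 and 90. A parabola over that span cannot fall sharply between the first two points and then recover, yet day 1 is where the trial expects its effect.

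An odds ratio near 1 could then be reported as no effect on cognitive trajectories when it mainly reflects how the model was set up.

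**Working it through.** **The plan's own figure.** The trajectory section gives no number, so the check uses the design effect from Sample Size: 15% versus 5% major disorder at day 1, two-sided 0.05, 80% power.

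n per arm = [1.96√(2·0.10·0.90) + 0.842√(0.15·0.85 + 0.05·0.95)]² / 0.10² = 140.1, so 141 per arm and 282 in total. Then 282/0.9 = 313.3, so 314. The stated sizes reproduce.

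**Step 1: what the classes have to explain.** Within class k the model is Z_it = β0k + β1k·t + β2k·t² + error. Baseline Z has variance 1 by construction. With an assumed within-patient correlation ρ of 0.5 to 0.8, stable between-patient variance summed over seven visits is 7ρ = 3.5 to 5.6. Suppose 10% of patients (the average of 15% and 5%) drop 1.96 SD at day 1 only. That adds 0.10·0.90·1.96² = 0.35 at one visit, about a tenth to a sixteenth as much. A likelihood-based class search will mostly follow the larger component.

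**Step 2: simulation of the planned model.** Settings: 282 patients, quadratic time, 1 to 8 classes, BIC with the 5% rule, ρ from 0.5 to 0.8, time in days or by visit number, 10% of patients dropping 1.96 SD at day 1 (isolated, or recovering by day 30), 8 replicates per setting.

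| Quantity | Range over settings |
|---|---|
| Classes chosen (mean) | about 4 to 5 |
| Baseline-score variance explained by class | 45-75% |
| Baseline-to-D1 change explained by class | 1-4% |
| Dropper status explained by class | 2-11% |
| Largest fitted D1 drop in any class (mean) | 0.00-0.16 SD |

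**Step 3: can a quadratic follow the dip?** Least-squares quadratic fits to three assumed mean curves at the seven visits. Curve A is 0, -0.92, -0.75, -0.35, -0.15, -0.05, 0. Curve B is an isolated -1.96 at D1. Curve C is 0, -1.96, -1.5, -0.75, -0.3, 0, 0. Entries are the fitted baseline-to-D1 change in SD.

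| Time scale | A (true -0.92) | B (true -1.96) | C (true -1.96) |
|---|---|---|---|
| Days | +0.02 | +0.03 | +0.05 |
| Visit number | -0.16 | +0.14 | -0.32 |
| log(day+1) | -0.08 | +0.15 | -0.16 |
| Square root of day | +0.04 | +0.18 | +0.11 |

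In days, curve A is fitted as -0.54 at baseline and -0.52 at D1. For B, R² is 0.13 to 0.17 and no scale shows a fall. The best case, C by visit number, keeps about one sixth of the fall (0.32/1.96).

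**Step 4: does each feature matter?** With 15% versus 5% dropping 1.96 SD by arm, ρ = 0.7, 1 to 6 classes and 60 replicates, a test of arm by class reached p < 0.05 as follows. The ranges cover dip shapes B and C.

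| Version | Runs with p < 0.05 |
|---|---|
| As planned, in days | 7-12% |
| Level scores with baseline, free mean per visit | 13-20% |
| Change from baseline, free mean per visit | 37-38% |
| Baseline-adjusted scores, free mean per visit | 27-48% |

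Freeing time alone helps a little; removing the baseline level as well helps more. With 60 runs the simulation standard error is about 4 points near 10% and 6 points near 40%, so only the ordering should be used.

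**The case against.** **The visits are analysed elsewhere.** A reader might infer that the repeated measurements are wasted, or that the trial could miss the effect it was sized for. The protocol does not support that. Primary Analysis tests day-1 incidence directly. Major disorder at D2, D7, D15, D30 and D90 is a secondary endpoint, defined as a decrease in Z score and compared by arm under Secondary Analysis. This stands, and it limits the point to one secondary objective.

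**Secondary Analysis may cover the trajectory endpoint.** It gives t or rank tests for continuous endpoints and promises mean differences for all outcomes. But it names no cognitive score or visit, and trajectories have their own section with their own treatment estimate. The generic sentence does not repair that section.

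**The GBTM may be meant for slow, lasting patterns.** For an illustrative decline of 0, -0.1, -0.2, -0.4, -0.6, -0.7, -0.8, a quadratic gives R² of 0.93 in days and 0.99 by visit number. The expected trajectories are in Figure 1, which cannot be seen here. This stands: the shape problem concerns early transient falls, not every trajectory. It does not answer the sorting by baseline level.

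**The time scale is open.** By visit number curve A becomes a visible shallow U (R² 0.46), so it would be too strong to say that the dip always vanishes. The fitted day-1 fall is still about a sixth of the true one (0.16/0.92).

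**A mixed model may not be much more powerful.** A reader might infer that it would detect the effect almost surely. That would need an assumed shift in every patient's mean, whereas the protocol gives only incidences. If 15% versus 5% of patients drop 1.96 SD, a baseline-adjusted day-1 comparison with 141 per arm has only about 34-51% power for ρ of 0.5 to 0.8. The case for it is that it estimates the right quantity, not that it guarantees detection.

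**Conclusion.** The point holds for the secondary trajectory objective. The protocol itself fixes level scores, baseline as an outcome point, at most quadratic time, and arm only as a predictor of class, so these are not details left to a later analysis plan. Sorting by baseline level is an expected result rather than an algebraic certainty; it held throughout the assumed correlation range. Poor fit to an early transient fall held on all four time scales tried, and is complete for an isolated day-1 drop. The correlations, dip shapes and dip sizes are assumptions, and the replicate counts are small. A null odds ratio for arm from this model should not be read as evidence against an effect on early recovery. The primary analysis, the sample size and the per-visit incidence comparisons are unaffected. The change should be made, but the trial's main conclusion does not depend on it.

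**What to change.** - **Treatment comparison.** Use a longitudinal mixed model of the common 22-point T-MoCA score (the T-MoCA items of the MoCA at in-hospital visits). Treat visit as a category, include an arm-by-visit interaction, and adjust for baseline as a covariate or through a common baseline mean. Report the arm difference with a 95% confidence interval at each visit.
- **GBTM.** Keep it as a descriptive analysis. Run it on post-operative change from baseline or on baseline-adjusted scores, with visit-coded or spline time. A quadratic in log(day+1) is not enough: for curve A it shows -0.08 of a true -0.92. State the time scale.

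The cost is a revision of the statistical section, one additional standard model and a lesser role for the GBTM. No new data are needed, because the protocol already plans to take the T-MoCA part from the MoCA.
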